## Abstract

**Background:**

Delirium is a frequent, costly and morbid problem. No agent has been shown to modify the natural history of the condition, and current treatments have significant side effects. Prophylactic melatonin in low doses has been shown to prevent delirium developing. This trial then aims to determine the feasibility of a trial to assess if melatonin at a moderate dose effectively treats the symptoms of delirium and modifies the natural history, including abating symptoms after treatment cessation.

**Methods/design:**

Elderly (≥70 years of age) patients admitted to the Royal Melbourne Hospital with delirium, and not requiring surgery, will be identified from the current practice of the investigators and through referral by other general medical unit staff. To facilitate this, other staff will be briefed on the project by investigators. Patients will be recruited with suitable informed and documented consent (person responsible) by the study investigators. They will receive orally either 5 mg melatonin (18 patients) or placebo (18 patients) nightly for 5 nights (or until discharged).

During treatment, participants will be assessed by study staff using a validated scale of delirium severity (the Memorial Delirium Assessment Scale), and a validated measure of delirium state (Confusion Assessment Method) to determine if melatonin decreases the severity or the duration of delirium. Assessment will continue for a further two days after treatment has ceased, to determine if the treatment causes persisting abatement of symptoms, and to assess for adverse events.

**Discussion:**

The on-going study described herein will contribute to our knowledge of available treatment options for elderly inpatients with delirium, where current pharmacological interventions show weak or no effect on hastening the resolution of delirium. As melatonin is safe, cheap, and potentially effective, it would be easily implementable in routine practice and could lead to significant outcome benefits for delirious inpatients.

**Trial registration:**

The trial is registered with the Australia New Zealand Clinical Trials Registry (trial ID: ACTRN12614000101684) (registered 28/01/2014).

## Background

Delirium is a clinical syndrome of acute onset characterised by fluctuating attention and awareness with a disturbance in cognition due to the direct physiological consequence of a medical condition, intoxication, withdrawal, toxin, or multiple aetiologies [1]. Melatonin (N-acetyl-5-methoxytryptamine) is a hormone (and likely neurotransmitter) produced by the pineal gland in the human brain. It is involved in sleep/wake cycle regulation. Delirium is a condition with little research into the underlying mechanism, but felt to be most commonly related to abnormalities of brain neurotransmitters.

**Table 1 Tab1:** Schedule of Procedures

Procedure	Entry (D0)	Daily 1–5 (on treatment)	Day 6	Final Visit (Day 7)
Consent	○			
Age	○			
Gender	○			
Electrolytes	○			
Liver function	○			
MMSE	○	○	○	○
Digit Span	○	○	○	○
CAM	○	○	○	○
MDAS	○	○	○	○
Motor type	○			
CMI	○			
IQCODE	○^a^			
GDS-15	○			
Katz ADL	○			
Presence of Restraints		○	○	○
# Falls		○	○	○
# Pressure areas	^b^	○	○	○
Rescue medication		○	○	○
Adverse events			○	○
Review INR	○^c^	○^c^		

^a^Ideally the IQCODE will be measured at entry but can be measured at any point

^b^Initial number and location will be recorded at entry in order to derive the number of new areas at each subsequent visit

^c^If participant is on warfarin, we will review the INR that has been performed every 1–2 days as is standard protocol for acutely unwell inpatients when warfarinised

Delirium is a common clinical phenotype with a variety of potential precipitating factors on the background of predisposing factors. The clinical phenotype does not appear to vary with cause [2], and therefore research into the treatment of delirium can be conducted without reference to aetiology. An exception is Delirium Tremens, a specific syndrome caused by withdrawal from chronic alcohol consumption. This is regarded separately from delirium and is not the topic of the proposed study.

One common feature of delirium is a disturbance of the sleep wake cycle [2]. In support of a potential role of melatonin and disturbance of melatonin metabolism in delirium, Balan et al. demonstrated that levels of urinary metabolites of melatonin were altered in delirium, in coordination with the level of psychomotor activity (low in those with hyperactive delirium, high in hypoactive delirium) [3]. Other studies have shown abnormalities of tryptophan (from which melatonin is formed) are associated with postoperative and critical care delirium [4, 5]. Further, case reports of successful melatonin use for the treatment of delirium have been published [6].

The hypothesis that melatonin might be useful for the prevention and treatment of delirium has been tested, with two trials being particularly relevant. Al-Aama et al. randomised 145 recently hospitalised participants in a medical service to melatonin 0.5 mg nocte or placebo for 14 nights or discharge [7]. Delirium diagnosis was assessed with the validated Confusion Assessment Method tool and severity by the validated Memorial Delirium Assessment Scale (MDAS). Delirium was clinically and statistically significantly reduced in the active treatment group by approximately 61 %, by 81 % when incident (pre-existing prior to enrolment) delirium was excluded, and 81 % when dementia and comorbidities were controlled for. By comparison, no medication has been shown to prevent delirium occurrence, and two trials of non-pharmacological treatments showed reductions in the order of 33 % [7]. Delirium severity (on MDAS) was not significantly different, and surrogate outcomes that would suggest efficacy in treatment of delirium such as length of stay, restraints and use of sedatives were also not significantly different.

A second trial examined melatonin 5 mg in prevention of delirium in elderly patients undergoing hip arthroplasty and spinal anaesthesia. 222 patients were randomised to standard treatment, midazolam prior to and post-surgery, or melatonin 5 mg prior to and post-surgery [8]. Delirium was assessed based on decline on the Abbreviated Mental Test from baseline. This methodology has been shown [8] to be a sensitive but not specific method of delirium detection, and likely inferior to the CAM. Delirium occurred in 16/49 control group participants, and 5/53 melatonin group participants, a 72 % relative risk reduction. Although the paper stated melatonin 5 mg was effective in the treatment of delirium, it was not clear how it was evaluated, and personal communication with the author revealed this statement was based on the clinical impression of psychiatrists assisting in the management of delirious patients.

In contrast to these two trials, a recently completed randomised-controlled trial of melatonin 3 mg in the prevention of delirium after hip fracture did not show a significant reduction in the incidence of delirium, nor in the severity of incident delirium [9].

Based on current knowledge, it is plausible that melatonin is useful for the prevention of delirium in elderly patients, that low dose melatonin does not appear to be useful for treatment of delirium, and that high dose melatonin (5 mg) may be effective in the treatment of delirium. However, this needs to be examined further before it can be recommended.

When considering the efficacy of melatonin in the treatment (rather than prophylaxis) of delirium, it should be noted that delirium abatement is regarded purely clinically. Were this decrease or cessation of symptoms to occur after cessation of an effective treatment, compared to standard care, it would constitute evidence of cure. This could be assessed by following trial participants after cessation of active and placebo treatment.

This paper describes the design of the study, “Moderate dose melatonin for the abatement and treatment of delirium in elderly general medical inpatients”, a trial currently in progress.

## Methods and design

This trial was designed based on CONSORT guidelines [10]. For a schematic detailing the layout of the study, see Fig. 1. Trial procedures are described in Table 1.

**Fig. 1 Fig1:**
[figure not shown]
Overview of the study protocol

### Research questions

#### Primary research question

To determine if melatonin of 5 mg nightly for 5 nights decreases the severity of symptoms of delirium in elderly medical inpatients by evaluation of the MDAS

#### Secondary research questions

Abatement of symptoms that continues for 2 further days after the 5 days of treatmentThe severity and duration of deliriumReduces fallsReduces pressure areasReduces the use of rescue medications (antipsychotics, benzodiazepines)Improves sleep quality as evaluated in Item 10 of the MDASReduces the presence of restraints

### End points

#### Primary

Change in MDAS score from baseline to average over days 1–5

#### Secondary

Change in MDAS score from average over days 1–5 to average over days 6–7Presence or absence of delirium from days 1–7 as assessed by CAM criteriaNumber of falls over days 1–5 of the study periodNumber of pressure areas developing over days 1–5 of the study periodNumber and dose of rescue medications used over days 1–5 of the study periodChange in score on item 10 of the MDASNumber of instances of the use of restraints over days 1–5 of the study period

### Location and setting

The Royal Melbourne Hospital in Parkville, Australia. It is a major teaching hospital with over 60,000 emergency attendances and over 85,000 patient admissions a year into 330 acute beds [11].

### Study population and recruitment

During multidisciplinary meetings and the day-to-day duties of investigators, potential patients will be considered for inclusion. Patients with a diagnosis of delirium via the CAM and who are 70 years or older as general medical inpatients will be screened according to exclusion criteria. These exclusion criteria include solely hypoactive delirium (MDAS question 9), planned surgery, the inability to speak or understand English, severe sensory impairment or dysphasia, an expected prognosis or discharge of less than 7 days, severe hepatic failure (defined as Bilirubin ≥2.5 times upper limit of normal; alkaline phosphatase, aspartate transaminase and/or alanine transaminase > 3 times upper limit of normal), a markedly non-therapeutic INR (<1 or >4), use of melatonin or melatonin receptor agonist in the preceding 14 days, active seizure disorder (a seizure in the last month, or a seizure disorder not on anticonvulsants), and concomitant cimetidine use. As melatonin is a sedative medication, it’s clinically inappropriate to provide this to patients who have an exclusively hypoactive delirium as this may exacerbate the decreased conscious state. Also, as per Balan et al. [3], an exclusively hypoactive delirium may be associated with an elevated melatonin level. Patients who have surgery planned during the study period are to be excluded as surgery and anaesthesia are independent risk factors for delirium and would act as intra-intervention confounders.

Given patients with delirium are unable to provide informed consent, consent will be obtained by the person responsible for surrogate decision making and documented on clear consent forms. The surrogate decision maker retains the capacity to withdraw the patient from the trial at any time. If during the course of the trial the patient regains capacity due to the resolution of their delirium, a separate informed consent will be obtained should the patient wish to continue; if they do not, they will be withdrawn from the trial.

The Melbourne Health Human Research and Ethics Committee has evaluated and approved this trial.

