### Statistics

Data will be collected for each patient on a daily basis, up to 7 days following recruitment. The primary and secondary outcome measures will be compared using standard statistical methodology. For continuous variables, results will be compared using a Students’ t-test with significance set to 0.05 if they are normally distributed, else a Mann-Whitney or other non-parametric test will be utilised. Control and treatment group homogeneity will be tested with Chi-square statistics. For discrete outcomes, results will be tested using a Chi-square test. Risk ratios will be employed where appropriate. The Hausman specification test will be used to determine whether the data should be analysed using either fixed or random effects, though it is expected that a random and fixed (mixed) effects model will be required.

Extensions to the statistical methods above may be required depending on what is found once the data is collected and the analysis is begun.

Missing data will be accounted for using the last observation carried forward method, and all data will be analysed according to the intention-to-treat principle primarily (and per-protocol analysis secondarily).

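### Patients who regain capacity and do not wish to continue leave the whole trial, with no option to stop capsules but keep assessments or chart data, so missing data depend on recovery

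*Protocol article*

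**What the plan says.** Consent comes first from a surrogate. Under Study population and recruitment the protocol then sets a trigger: "If during the course of the trial the patient regains capacity due to the resolution of their delirium". Once that happens, one of two things follows: "a separate informed consent will be obtained should the patient wish to continue; if they do not, they will be withdrawn from the trial". The surrogate has a parallel power: "The surrogate decision maker retains the capacity to withdraw the patient from the trial at any time". In neither case does the article separate stopping the study capsules from ending assessments or use of chart data.

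Several endpoints need data after recovery:
- The primary endpoint is "Change in MDAS score from baseline to average over days 1–5".
- Two secondary endpoints are the MDAS change from the days 1–5 mean to the days 6–7 mean, and CAM status over days 1–7.
- Falls, new pressure areas, rescue medication and restraints are endpoints over days 1–5.

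The Methods/design paragraph of the abstract adds: "Assessment will continue for a further two days after treatment has ceased". The aim there is to see whether abatement persists. Data collection states that rescue medication is obtained by chart review.

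The Statistics section fixes how gaps are filled: "Missing data will be accounted for using the last observation carried forward method". On the analysis set the same section says: "all data will be analysed according to the intention-to-treat principle primarily". Power analysis allows 10% dropout in total and arrives at 18 per arm.

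**The concern.** The gate to this exit is the outcome under study. A patient still delirious is never asked; a patient who has recovered is. Followed as written, the rule therefore ends data collection by this route only among recoverers.

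These are the patients in whom persistence or relapse can be observed. The Background describes delirium as being of "acute onset characterised by fluctuating attention and awareness", so an early recovery need not last. Data collection dates the end of delirium to the last CAM-positive visit, so a recoverer who leaves has the duration closed with no later visit at which a relapse could be seen.

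A recovered patient may simply not want more capsules, or more daily cognitive testing, and have no objection to the rest. Under the two-way wording that patient is lost for the remaining days of the primary mean, for days 6–7 MDAS and for days 1–7 CAM. If the exit comes before day 5, part of the event counts goes too. An analysis plan cannot recover data that were never collected.

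**Working it through.** **Plan's own figure.** For a 3-point difference, SD 3.0, 80% power and two-sided 5%: n = 2 × (1.96 + 0.84)² × 3.0²/3² ≈ 15.7, so 16 per arm. Then 16/0.9 = 17.8, so 18. The stated size reproduces. It does not decide this point, but it fixes the allowance: 10% of 18 = 1.8 per arm, or 3.6 of 36.

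**Inputs not in the documents (assumptions).** Recovery r = 50% active, 30% placebo. Share q of recovered patients who decline = 25% or 50%, equal in both arms. Days 6–7 MDAS is 4 if recovered and 10 otherwise.

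**Losses by this route** = 18 × r × q.
- q = 25%: 18 × 0.5 × 0.25 = 2.25 and 18 × 0.3 × 0.25 = 1.35. Total 3.6 of 36, exactly the 10% allowance.
- q = 50%: 4.5 and 2.7. Total 7.2 of 36, or 20%.
- If recovery is the same in both arms, the losses are the same too.

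**Days 6–7 mean difference, full data.** Active 0.5 × 4 + 0.5 × 10 = 7.0; placebo 0.3 × 4 + 0.7 × 10 = 8.2; difference −1.20.

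**Under LOCF, recovered score recorded before exit and recovery lasts.** Decliners carry 4, which is also their true value. The difference stays −1.20.

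**Under LOCF, last recorded score still delirious.** Decliners carry 10, so mean = r(1−q) × 4 + [1 − r(1−q)] × 10.
- q = 25%: active 0.375 × 4 + 0.625 × 10 = 7.75; placebo 0.225 × 4 + 0.775 × 10 = 8.65; difference −0.90.
- q = 50%: active 0.25 × 4 + 0.75 × 10 = 8.50; placebo 0.15 × 4 + 0.85 × 10 = 9.10; difference −0.60.

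This between-arm mean is only an illustration. The listed secondary endpoint is the change from the days 1–5 mean.

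**Primary endpoint, allowing relapse.** A simulation used 200,000 patients per arm, baseline MDAS 11.4 (SD 3.0), daily recovery probability 0.10 placebo v 0.20 active, MDAS 7 points lower while recovered, and refusal at first recovery. It gave these between-arm differences:

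| Daily relapse | Decline | Full data | LOCF, recovered day scored | LOCF, recovered day not scored |
|---|---|---|---|---|
| 0.10 | 25% | about −1.24 | −1.27 | −0.93 |
| 0.25 | 25% | −1.05 | −1.13 | −0.79 |
| 0.25 | 50% | about −1.05 | −1.23 | −0.52 |
| 0.40 | 25% | −0.90 | −1.02 | −0.68 |

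At 0.25 relapse, withdrawals were 13% v 20% (25% declining) and 26% v 40% (50% declining). For the listed days 6–7 change, with 25% declining, full data gave about −0.12 and LOCF gave −0.21 or −0.09. The carried value exaggerates the effect when it hides relapse and shrinks it when it hides recovery.

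**The case against.** The strongest objection is that this is one consent sentence in a condensed article. Levels of withdrawal are usually set out in the full protocol and consent form, which are not shown, and the article does not say what happens to chart data or to data already collected. That caution stands for those details. It does not dispose of the point, because the article states a positive rule with two outcomes, and withdrawal from the trial in its ordinary meaning ends collection.

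Four stronger readings are tempting, and the documents do not support them:
- *Recovery itself removes patients.* It does not. Loss needs recovery and then the patient's own refusal, which must be respected.
- *More patients are necessarily lost on melatonin.* That requires faster recovery on melatonin and similar refusal rates. With equal recovery there is no imbalance.
- *The rule dilutes the treatment effect.* Dropping decliners on the same inputs gives 7.43 − 8.54 = −1.11 (25%) or 8.00 − 8.94 = −0.94 (50%), which looks like dilution. The plan does not drop them; it carries values forward, and the direction then depends on which score was last recorded.
- *The rule contradicts intention-to-treat.* Not literally. Patients stay in the analysis set, but with carried values in place of observations.

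It also stands that the event endpoints cover days 1–5 only, so later exits cost them nothing; that only rescue medication is expressly chart-based; and that every recovery and refusal rate here is assumed.

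**Conclusion.** The point holds as a weakness in the collection rule. Data loss by this route is confined to patients whose delirium has resolved, and it differs by arm if recovery differs and refusal rates are similar. LOCF substitutes for the lost values without correcting them, and the sign of the bias cannot be predicted.

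The documents do not allow the size to be fixed. On the assumed rates, the distortion of the days 6–7 mean difference runs from nil (−1.20 retained) to a halving (−0.60). The simulated primary difference moves from about −1.05 to between −1.23 and −0.52. At 25% refusal this single route uses the whole 10% dropout allowance; at 50% it uses twice that. At low refusal the effect is small. It should be changed because the remedy is cheap and the days affected are those on which persistence of benefit is to be judged.

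**What to change.** At the recovered-capacity consent, and when a surrogate withdraws a patient, offer graded options in place of the two-way rule:
1. Continue fully.
2. Stop study capsules but continue the scheduled assessments to day 7.
3. Stop visits but allow use of routinely charted data (at least rescue medication) and of data already collected.
4. Withdraw fully.

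Where the patient agrees, complete that day's scheduled CAM and MDAS, so that the last recorded score reflects the state at the decision. Record the option chosen. Full refusal must be honoured without qualification.

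The cost is a longer consent form and a minor ethics amendment. The assessments to day 7 and the chart review for rescue medication are already scheduled. Recording the choices would also give the pilot refusal and retention rates for planning the larger trial.

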### Randomisation & blinding

After enrolment, patients will be randomised into treatment groups by drawing a sealed, opaque envelope from a box containing an allocation code (randomised by an unrelated statistician). The box contains equal numbers of allocation codes to a total of the expected number of participants. The envelope and code are discarded after being drawn. The envelopes will be in permuted blocks of 4 (2 placebo 2 active).

The results of this randomisation are not known to any of the investigators or intervention administration staff. A separate code interpretation sheet is kept locked in the trial pharmacy, where after the completion of data collection the allocation codes will be matched to provide the requisite placebo vs intervention information.

### Study medication and administration

Study medication tablets appear identical and are packaged in HDPE containers of 5 capsules each. They are prepared in accordance with Good Manufacturing Procedure (GMP) guidelines. On prescription by Medically qualified research staff, a container may be collected from the trial pharmacy upon inclusion of a patient. The medication was purchased through an unrestricted grant from Healthe Care Australia Pty Ltd. The medication is prescribed and administered as per the regular drug chart protocol at our institution, where it is marked as ‘nocte’. As such, to mirror normal practice, it is administered at approximately 8 pm nightly for five nights.

### Data collection

Baseline demographic data and current medication use (including as needed [PRN]) medications will be recorded. Following enrolment, patients will be visited by trained and qualified research staff every day to collect data and assess safety.

Delirium will be diagnosed using the Confusion Assessment Method (CAM) [12], as the primary outcome variable. This is a widely used instrument for the detection of delirium in the acute hospital setting. It has a sensitivity of 94–100 % and a specificity of 90–95 % and generates a DSM IV diagnosis of delirium. Duration of delirium will be recorded in days and delirium considered to have ceased the day of the last visit at which the participant was positive on CAM.

Delirium severity will be measured by the Memorial Delirium Assessment Scale (MDAS) [13], a validated scale suitable for use by both skilled clinical and trained observers, with good internal consistency and inter-rater reliability. The maximum MDAS score will be used as a measure of severity.

Comorbidity will be measured by the Charlson scale (Charlson Comorbidity Index, CMI) [14] from the history, patient, and/or surrogate; pre-morbid function will be measured using the Katz Activities of Daily Living (ADL) [15] index score from their condition two weeks prior to admission; depression will be measured using the GDS-15 item scale [16]; cognition will be measured by the mini-mental state examination (MMSE) [17].

Premorbid cognitive impairment will be determined both from chart review for a diagnosis of dementia or other cause of chronic cognitive impairment by a specialist neurologist, psychiatrist, or geriatrician, and the administration of the Informant Questionnaire for Cognitive Impairment or Dementia in the Elderly short form (IQCODE-sf) [18]. The IQCODE-sf will be completed with the assistance of primary caregivers.

Motor subtype of delirium does not have a validated scale and will be assessed by clinical judgement of the investigators.

Use of rescue medication will be determined from chart review and recorded by medication and average daily dose since last visit, and will be sub-stratified as required into groupings of those with significant anticholinergic activity, opioids, antipsychotics, and benzodiazepines.

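### Table 1 schedules adverse-event recording on none of the five treatment days, although the text says staff assess safety at every daily visit

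*Protocol article*

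**What the plan says.** Three places in the protocol article bear on when adverse events are recorded.

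- **Data collection.** Once enrolled, "patients will be visited by trained and qualified research staff every day to collect data and assess safety". This sets a daily frequency for safety assessment and exempts no day.
- **Table 1, Schedule of Procedures.** There are four visit columns: entry, the treatment days (heading beginning "Daily 1–5 (on treatment"), Day 6, and the Final Visit on Day 7. The "Adverse events" row has marks under Day 6 and the Final Visit only.
- **Abstract, Methods/design.** The assessments named during treatment are the MDAS and the CAM. The text then says "Assessment will continue for a further two days after treatment has ceased", and gives the purpose as "to determine if the treatment causes persisting abatement of symptoms, and to assess for adverse events". This is the abstract's only mention of adverse events.

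**The concern.** A schedule of procedures is what ward staff usually work from. Here it asks for no adverse-event entry while participants are taking the study drug, and the text asks for safety to be assessed daily. Staff cannot follow both as written.

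The treatment period matters most for this purpose. Under Study population and recruitment, the article describes melatonin as sedating and excludes purely hypoactive delirium on that ground. Treatment can also end early. The abstract allows dosing to stop at discharge, and the consent arrangements allow withdrawal by the surrogate or by a patient who regains capacity. Such a participant could take several doses and leave before the first visit at which Table 1 schedules an adverse-event record.

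**Working it through.** The article gives no figure for this point, so there is none to reproduce. The check is a reading of Table 1 row by row, set against the text.

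**Step 1: the marks in Table 1.**

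| Row | Entry | Days 1–5 | Day 6 | Day 7 |
|---|---|---|---|---|
| Presence of restraints | – | marked | marked | marked |
| Falls | – | marked | marked | marked |
| Pressure areas | footnote b | marked | marked | marked |
| Rescue medication | – | marked | marked | marked |
| Adverse events | – | **blank** | marked | marked |
| INR review (warfarin users) | marked | marked | – | – |

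The adverse-event row starts one column later than "Rescue medication" directly above it. The neighbouring rows sit in their expected columns, so a general shift of the table does not explain the blank.

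**Step 2: count the days.** Adverse events are scheduled on 0 of 5 treatment days and 2 of 2 post-treatment days, that is, on 2 of the 7 days after entry. The Data collection sentence implies 7 of 7.

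**Step 3: do other items fill the gap?** Falls, pressure areas, restraints and rescue medication are recorded on each treatment day, but each is a specific item, and all four appear among the secondary end points. The INR item is restricted: "If participant is on warfarin, we will review the INR that has been performed every 1–2 days". Table 1 lists adverse events as a row of their own, so the schedule itself treats them as distinct from these items.

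**Step 4: is there a look-back?** For rescue medication, Data collection names a source (the chart) and a reference period (since the previous visit). No such statement says that the Day 6 or Day 7 adverse-event record covers days 1–5.

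**Step 5: who could be missed?** Power analysis plans 18 per arm, 36 in all, with 10% dropout: 0.10 × 36 = 3.6, or about 4 participants. The article does not say when dropout is expected, so this is not an estimate of the number leaving before day 6. It is only the one planning figure available.

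**The case against.** The strongest reply is that Data collection already states the sensible practice. On that view Table 1 has one cell wrong, and staff who visit daily to assess safety will record what they find. That may well be what happens. It still relies on the sentence that the schedule contradicts, so it supports correcting the cell rather than leaving it.

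A second reply is that a journal article condenses a fuller protocol. That is a fair answer to any complaint about missing definitions, onset dates or between-arm event comparisons, and none is made here. It does not cover a visit-by-visit schedule that the article prints and that disagrees with its own text.

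Several stronger readings are tempting, and the article does not support them:

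- *Safety goes unobserved on treatment.* It does not. Besides the items in the table above, MMSE, CAM and MDAS are done daily, and MDAS question 9, which the article uses to identify hypoactive presentation, gives some daily indication of over-sedation.
- *The abstract confirms that adverse events are assessed only after treatment.* It gives a reason for continuing assessment for two more days. It mentions adverse events only there, but does not exclude them earlier.
- *Events would come only from the recall of delirious patients, biasing the result toward no harm.* No source for adverse-event data is stated. These are inpatients with charts, seen daily. Incomplete recording is a risk if the table is followed, and its direction is not shown.
- *A large share of participants would be missed.* An exponential stay with an assumed mean of 10 to 14 days would give 1 − exp(−5/10) = 0.39 to 1 − exp(−5/14) = 0.30 leaving by day 5. That model puts its highest leaving rate in the first days, yet the exclusion criteria remove patients expected to be discharged within 7 days. The 14-day stay quoted in Power analysis comes from the Canadian trial, not from this hospital. The figure should not be used.

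**Conclusion.** The contradiction is real and limited. As printed, Table 1 schedules general adverse-event recording on none of the five treatment days, and Data collection requires daily safety assessment. If the table is followed, on-treatment adverse events may be incompletely recorded, and participants who leave before day 6 have no scheduled adverse-event record. The count of 0 in 5 rests only on the position of the marks in the table's extracted text. A misplaced mark cannot be wholly excluded, but the alignment of the other rows makes it unlikely. The number of participants affected cannot be derived from the article.

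No research question or end point concerns adverse events in general, so the consequence is confined to the completeness of the on-treatment safety record.

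**What to change.** Mark the adverse-event row under the days 1–5 column of Table 1, so that events are recorded at each daily visit on days 1–7 as Data collection implies. Optionally, reword the abstract sentence so that adverse-event assessment is not mentioned only for the two days after treatment. Because the article describes a trial already in progress, it would help to state which of the two instructions staff have been following.

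The cost is one table cell and, if wanted, one sentence. Research staff already visit every day, so no visits are added and the extra recording is small.
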